#### 2.4.3. Other Outcomes

To examine the effects of usage behavior on primary and secondary outcomes, system usage data regarding the participation in the health programs during the intervention phase (frequency (days with logins/week) and duration of program logins (average minutes/login), logged activities (activities/week) (intervention group)) and the follow-up phase (frequency of program logins (days with logins/week)) will be collected and stored by VHG. A secure cloud system will be used to transfer these data to the DoSS [71].

### 2.5. Participant Timeline

As the study participant flow of the clinical trials (F_clin_, W_clin_) combined with the online trials (F_online_, W_online_) is complex, its illustration is divided into the enrolment process (Figure 3a) and the intervention and assessment process (Figure 3b). Further details of the study participant flow of the online trials are described in another study protocol [71].

### 2.6. Sample Size

The sample sizes of the clinical trials (F_clin_, W_clin_) were calculated with regard to the long-term effect (t0–t3) of the respective primary outcome (F_clin_: VO_2_max, W_clin_: body weight) using G*Power software (Version 3.1) (Heinrich-Heine-Universität Düsseldorf, Düsseldorf, Germany) [109]. Based on comparable studies [50,110,111], effect sizes of Cohen’s *d* = 0.45 (F_clin_) and *d* = 0.50 (W_clin_), as well as a significance level of 0.05 and a statistical power of 0.80 were assumed. For the fitness trial (F_clin_), this resulted in a required case number of *n* = 79 for both the intervention and control groups. For the weight loss trial (W_clin_), the required case number was *n* = 64 for both study groups. Allowing for an additional dropout rate of 15% in each trial, the total target sample size was found to be *n* = 186 (93 + 93) (F_clin_) and *n* = 150 (75 +75) (W_clin_). Due to limited resources, there are no plans to exceed these sample sizes. Details can be found in the study protocol of the online trials [71].

### 2.7. Recruitment

The recruitment period for the clinical trials (F_clin_, W_clin_) is planned from January to June 2020. To achieve the target sample sizes, extensive recruitment measures will be carried out in the southwest of Germany (postcode area: 79) using a wide range of print and online media. These will mainly include local press and radio campaigns, flyers displayed in regional shops and centers, and Google advertisements. In addition, the institutions involved in the project will draw attention to the trials on their websites, newsletters, and social media. The recruitment process will be monitored to initiate appropriate measures if the required sample sizes are not reached by the planned end of the recruitment.

From recruitment to successful study enrolment, subjects will have to pass through a multistep process (Figure 3a). If subjects become aware of the study, they will be guided to the project’s landing page, first selecting their personal health goal. Afterwards, they will receive the study information for the respective online trial (F_online_, W_online_), provide written consent, and thus successfully register for the online trial. The study participants will then obtain the first online questionnaire by e-mail. After completing the questionnaire, the study participants from the postcode area 79 will be invited for the respective clinical trial (F_clin,_ W_clin_). To register for the clinical trial, they will have to agree to the study information (Supplementary Materials Files S1 and S2) by their written consent form (Supplementary Materials Files S3 and S4) and enter their contact details and time of availability. After successful registration, they will be randomized in the clinical trial. Within a few days, the study staff will contact the study participants by telephone or e-mail to provide more detailed study information, conduct a complete screening according to the inclusion and exclusion criteria, and make an appointment for the first medical examination. If the criteria are not met, the subjects will not be admitted to the medical examination. Still, they will remain randomized within the clinical trial and participate in the online trial. Within the first on-site medical examination, the eligibility criteria will be rechecked, and any outstanding questions will be answered. After a 7-day follow-up measurement of physical activity and dietary behavior, the baseline assessment and thus the study enrolment will be completed.

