## Abstract

Web-based lifestyle interventions have attracted considerable research interest. Available evidence on such interventions suggests health-promoting effects, but further research is needed. Therefore, this study aims to investigate short-, medium-, and long-term health effects of a web-based health program (“TK-HealthCoach”, TK-HC) offered by a national statutory health insurance fund (Techniker Krankenkasse, TK). The study comprises two randomized controlled clinical trials to evaluate the health goals “Increasing Fitness” (F_clin_) and “Losing and Maintaining Weight” (W_clin_). A total of *n* = 186 physically inactive (F_clin_) and *n* = 150 overweight or obese (W_clin_) adults will be randomly assigned to a 12-week interactive (TK-HC) or non-interactive web-based health program using permuted block randomization with a 1:1 allocation ratio. Primary outcomes include cardiorespiratory fitness (F_clin_) and body weight (W_clin_). Secondary outcomes comprise musculoskeletal fitness (F_clin_), physical activity and dietary behavior, anthropometry, blood pressure, blood levels, and vascular health (F_clin_, W_clin_). All outcomes will be measured before and after the 12-week intervention and after a 6- and 12-month follow-up. Additionally, usage behavior data on the health programs will be assessed. Linear mixed models (LMMs) will be used for statistical analysis. Findings of this study will expand the available evidence on web-based lifestyle interventions.

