#### 2.3.2. Non-Interactive Web-Based Health Program

The program for the control group for both clinical trials (F_clin_, W_clin_) will consist of a simply designed online platform that offers support in increasing physical activity and physical fitness (F_clin_) or losing and maintaining weight (W_clin_) over a 12-week intervention phase. In terms of content, it consists of a health-related knowledge transfer. Thus, only scientific background information on the respective health goal can be found, structured in short articles, but without interactive components. In addition, the user has access to personal data and the study information and consent form for the online and the clinical trial and has the option to withdraw participation from the trials and the health program.

The study participants of the clinical trials (F_clin_, W_clin_) will receive the respective health program after successful baseline assessment. They will log into the program via the project’s landing page. Criteria for discontinuing, interrupting, or modifying the allocated intervention are defined as feeling unwell, worsening health status, illnesses, diseases, injuries, harms, adverse events, or withdrawal from participation. These criteria will be determined by the study participant or the principal medical investigator of the study. Apart from the interventions, the participant will not be allowed to participate in other studies on physical activity or dietary behavior. For successful study participation and to promote adherence, the study participants will get free medical examinations and an activity tracker (Fitbit Charge 3^TM^) [74]. For participating in the online trial, they will obtain a shopping voucher and discount coupons. Apart from that, all study participants will be given free access to the current version of the TK-HC, including all coaching modules after study completion. As the TK-HC was frozen as a study version before the study started, the current version of the TK-HC contains some new content or features as it is continuously developed [71]. To maintain adherence during the study course, the study participants of the clinical trials will be reminded of the medical examinations by telephone and e-mail. To further monitor adherence, usage behavior data on the health programs will be analyzed within the formative evaluation of the online trials [71].

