## 3. Materials and Methods: Assignment of Interventions

### 3.1. Allocation

To achieve study groups of approximately the same size in each clinical trial (F_clin_, W_clin_), the study participants will be randomly assigned to the intervention and control group with a 1:1 allocation ratio by permuted block randomization with variable block sizes of 4, 6, and 8. The generation of the allocation sequences was done by SEVERA using the RITA software (Version 1.50) (Universität zu Lübeck, Lübeck, Germany) [112]. The randomization lists were sent to VHG via a secure cloud system and are securely stored there. This will ensure allocation concealment so that the randomization for each clinical trial will be implemented without any influence. If the study participants have successfully registered for the clinical trials on the project’s landing page, the randomization for each trial will be carried out in an automatic computer-based way according to the generated lists [71].

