According to the intention-to-treat (ITT) principle, all randomized cases will be included. In addition, only cases that have followed the per-protocol (PP) principle will be analyzed. While for ITT analysis, missing values will be imputed, in PP (complete case) analysis, only study participants with no missing values for the corresponding outcome will be analyzed. The ITT and PP analysis will be compared. An assessment of completed measurement time points will be used to test whether study participants who have completed all medical examinations differ in the corresponding outcome. Multiple imputation will be used to impute missing data in the ITT analysis. Influx and outflux statistics will be applied to identify factors that will serve as auxiliary variables for the imputation model. Sensitivity analysis will be performed to compare imputed with not imputed data.

The usage behavior data will be analyzed between the intervention and control group and within the intervention group. The analysis between the study groups will be done descriptively. For the analysis within the intervention group, the outlined model will be modified. Therefore, the group variable will be omitted, and a variable that codes usage behavior will replace the group variable in the model on level 2.

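### As written, the ITT analysis keeps ineligible, never-examined people and imputes their whole primary outcome, and the plan does not settle whether 186 and 150 count people randomised or people examined

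*Protocol article*

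**What the plan says.** **Order of events.** Section 2.7 places randomisation directly after web registration: "After successful registration, they will be randomized in the clinical trial". Section 3.1 confirms that this step needs no staff: "the randomization for each trial will be carried out in an automatic computer-based way according to the generated lists". Only in the following days do staff contact the person to "conduct a complete screening according to the inclusion and exclusion criteria". Eligibility is checked again at the first on-site visit.

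**Screen failures.** They are not admitted to the examination. Section 2.7 adds: "Still, they will remain randomized within the clinical trial and participate in the online trial".

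**Programme access.** Under section 2.3.2, clinical-trial participants "will receive the respective health program after successful baseline assessment".

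**Analysis set.** Section 4.3 states: "According to the intention-to-treat (ITT) principle, all randomized cases will be included". Missing values in that analysis are multiply imputed. A complete-case per-protocol analysis and a comparison of imputed with non-imputed data are planned as well.

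**Numbers.** Section 2.6 requires 79 per arm (fitness) and 64 per arm (weight), and then: "Allowing for an additional dropout rate of 15% in each trial, the total target sample size was found to be" 186 and 150. It foresees no recruitment beyond these figures. The Abstract attaches the same figures to randomisation: 186 and 150 "adults will be randomly assigned to a 12-week interactive (TK-HC) or non-interactive web-based health program". Section 4.1 expects on-site data at four time points on about 336 people.

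**The concern.** ITT analysis protects the comparison by keeping eligible people who stop, do not adhere or are lost. Here the rule also takes in people who do not meet the section 2.2 criteria and who, by section 2.7, never completed enrolment, because enrolment ends only with the baseline assessment. Both primary outcomes are measured only at the clinic. A person who fails the telephone screening therefore has no primary value at t0, t1, t2 or t3, and the entire series would be imputed, essentially from relationships seen in eligible people. That adds no information on the clinic outcome, makes the result depend more on the imputation model, and blurs the population to which the estimate applies. Section 4.2 also has personal data of excluded people deleted during screening, which sits awkwardly with keeping them in the analysis, although pseudonymised research data might remain.

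The second issue is the count. The same totals serve as the number randomised and as the number with clinic data. Both can be true only if no randomised person fails screening, and section 2.7 provides for such failures. Which count is meant decides whether the stated power is delivered.

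**Working it through.** **Inputs from section 2.6:** d = 0.45 (fitness) and 0.50 (weight), alpha 0.05, power 0.80, 15% dropout, targets 93 + 93 and 75 + 75. Sidedness is not stated; two-sided reproduces the figures and one-sided does not (it gives 62 and 51 per arm).

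**Step 1. Reproduce the plan.** A two-sided two-sample t-test (noncentral t) needs 78.49, so 79, and 63.77, so 64 per arm. Power at these sizes is 0.803 and 0.801. The plan's figures reproduce.

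**Step 2. What the 15% covers.**
- Fitness: 79 / 0.85 = 92.9, so 93. Back-check: 93 x 0.85 = 79.05 against 79 needed.
- Weight: 64 / 0.85 = 75.3, stated as 75. Back-check: 75 x 0.85 = 63.75 against 64 needed.
- Largest total loss compatible with the required numbers: 1 - 158/186 = 15.1% and 1 - 128/150 = 14.7%.

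Dropout alone uses the allowance. Nothing is left for losses between randomisation and t0.

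**Step 3. If the targets count people randomised.** Let s be the share failing screening after randomisation. The document gives no rate, so s is an assumption. Evaluable per arm = (93 or 75) x (1 - s) x 0.85, with power from the same t-test. Total to randomise = 2 x (79 or 64) / [0.85 x (1 - s)], rounded up per arm.

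| s (assumed) | Fitness: per arm, power | Weight: per arm, power | Total to randomise for 79 / 64 evaluable per arm |
|---|---|---|---|
| 5% | 75.1, 0.78 | 60.6, 0.78 | 196 / 160 |
| 10% | 71.1, 0.76 | 57.4, 0.76 | 208 / 168 |
| 20% | 63.2, 0.71 | 51.0, 0.71 | 234 / 190 |
| 30% | 55.3, 0.65 | 44.6, 0.65 | 266 / 216 |

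**Step 4. How much would be imputed.** The share of t3 primary values missing in the all-randomised set is 1 - (1 - s) x 0.85. At s = 20% this is 1 - 0.80 x 0.85 = 32%, and 20% of the set would have no measured primary value at any visit.

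**Step 5. If the targets count people examined.** Then 186 x 0.85 = 158.1 and 150 x 0.85 = 127.5 against 158 and 128 needed, so the stated power stands. The number randomised then exceeds 186 and 150 by however many fail screening, and the Abstract is wrong on that point. The never-examined people remain in the ITT set under either count.

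**The case against.** **The targets may well count people examined.** Section 4.1 ties the total to on-site data. Section 2.7 completes enrolment at baseline. Section 5.1 tracks registrations, telephone screenings and examinations before recruitment is closed, and the resource limit in section 2.6 fits clinic visits of several hours better than web registrations. This stands. A reader might infer that the trials are underpowered, but the documents do not establish it: the shortfall depends on which count is meant and on a failure rate that is not given. Registrants have already joined the online trial and completed its questionnaire, so failures could be few. The power figures above also use a simple t-test at t3, whereas the planned mixed model can use partial follow-up from dropouts. It gains nothing from people who were never examined.

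**Other analyses would expose the problem.** The complete-case per-protocol analysis leaves out never-examined people, and imputed and non-imputed results are to be compared. That partly answers the concern, but it leaves the ITT set itself unchanged. Section 4.3 never names a primary set. That ITT is the main analysis is inferred from its being stated first, with per-protocol as an addition.

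**Online-trial data could inform the imputation.** Screen failures stay in the online trial, which collects self-reported outcomes, so it would be too strong to say that their values come from nothing. Section 4.3 does not say that these data will be used, however, and self-report cannot stand in for VO2max or clinic weight at four visits.

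**All randomised is the recognised principle, and a separate analysis plan may refine it.** The first part is fair, and is why that analysis should be kept. On the second, the document already fixes the rule without exception, so this is a stated rule and not an omitted detail.

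**Excluding screen failures is not automatically unbiased.** A reader might assume it is, because section 3.2 plans blinded care providers and assessors and section 2.3.2 releases the programme after baseline. The latter does not cover people who never have a baseline, and section 3.2 admits that staff may learn the allocation. Leaving out eligible people who merely missed t0 is less clearly neutral than leaving out the ineligible.

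**Conclusion.** The concern holds in two parts.

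1. **Analysis set: firm.** Taken together, sections 2.7, 3.1 and 4.3 place ineligible people with no clinic measurement in the ITT analysis and impute their primary outcome at every visit. The number affected is unknown.

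2. **Sample size: conditional.** That the 15% allowance has no room beyond dropout is arithmetic. Power drops below 0.80 only if 186 and 150 are counted at randomisation: to about 0.76 at an assumed 10% screen failure and 0.71 at 20%, in both trials. If they are counted at examination, power stands and the Abstract needs correcting. The documents support either reading, so what is established is an unreconciled count and not a proven loss of power.

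A reader might also conclude that randomisation must be moved to after baseline. The documents do not support that as a change here. Recruitment was planned for January to June 2020, and screen failures continue in the linked online trial, which a later trigger could affect.

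**What to change.** Before outcomes are analysed, amend sections 4.3 and 2.6 and the Abstract:

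- Define the main ITT set as all randomised participants who were confirmed eligible by staff blinded to allocation, before programme access, and who had a t0 examination. Confirm from study records that both conditions (blinded confirmation, no earlier access) held in practice.
- Do not impute clinic outcomes for never-examined people in the main analysis.
- Report, by arm, the number failing screening after randomisation and, separately, the number eligible who missed t0.
- Keep the all-randomised imputed analysis as a sensitivity analysis.
- State that 186 and 150 count participants with a completed baseline and correct the Abstract; or state that they count people randomised and restate the power with the observed screen-failure share.

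The cost is about one paragraph of text and two extra rows in the participant flow. The small downside is that the main set becomes a modified ITT set rather than all randomised, which the sensitivity analysis and the by-arm counts make transparent. Randomising after confirmed eligibility and baseline is a lesson for a future trial.

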## 3. Materials and Methods: Assignment of Interventions

### 3.1. Allocation

To achieve study groups of approximately the same size in each clinical trial (F_clin_, W_clin_), the study participants will be randomly assigned to the intervention and control group with a 1:1 allocation ratio by permuted block randomization with variable block sizes of 4, 6, and 8. The generation of the allocation sequences was done by SEVERA using the RITA software (Version 1.50) (Universität zu Lübeck, Lübeck, Germany) [112]. The randomization lists were sent to VHG via a secure cloud system and are securely stored there. This will ensure allocation concealment so that the randomization for each clinical trial will be implemented without any influence. If the study participants have successfully registered for the clinical trials on the project’s landing page, the randomization for each trial will be carried out in an automatic computer-based way according to the generated lists [71].

### 3.2. Blinding

As the study participants of the clinical trials (F_clin_, W_clin_) will be informed about the interactive and non-interactive web-based health program, they will recognize which program they have been assigned to immediately after logging in. Thus, blinding the participants will not be possible. However, the healthcare providers and outcome assessors will be blinded, as they will only be informed about group allocation after all outcome assessments have been completed. Although the study participants will be asked not to mention their group affiliation during the on-site examinations, it is possible that the healthcare providers and outcome assessors will become aware of it. The data analysts of the clinical trials will not be blinded, as data will possibly reveal group membership [71].

## 4. Materials and Methods: Data Collection, Management, and Analysis

### 4.1. Data Collection Methods

Data of the clinical trials (F_clin_, W_clin_) will be collected on about 336 subjects at four measurement time points (t0, t1, t2, t3) at the DoSS. The feasibility of the data collection methods has been tested in pilot trials. The data will be collected in separated and protected premises by qualified staff using reliable and validated instruments with standardized procedures. The staff will be thoroughly instructed and trained on all measurements in a standardized manner. The data collection will be done using a case report form for each study participant. The study staff will carefully complete this form during the medical examinations, and the study director will subsequently review it to ensure high data quality. All data will be digitized and subjected to final plausibility checks. The system usage data collection methods are described in the study protocol of the online trials [71].

Various measures are planned to promote participant retention and complete follow-up to make data sets as complete as possible. First, for successful trial participation, the study participants will receive free medical examinations, an activity tracker (Fitbit Charge 3^TM^), a shopping voucher, discount vouchers, and free access to the current version of the TK-HC. Moreover, the participants will be reminded of each medical examination, and all examinations will be scheduled in advance. Furthermore, participant retention and usage behavior data will be monitored. The reasons for non-retention and non-adherence will be documented for data analysis and interpretation. If subjects do not adhere to the intervention protocols, all outcome data will still be assessed. For data analysis, however, non-adherent participants will be considered by including the usage behavior data.

